# Automated bolus advisor control and usability study (ABACUS): does use of an insulin bolus advisor improve glycaemic control in patients failing multiple daily insulin injection (MDI) therapy? [NCT01460446]

**DOI:** 10.1186/1471-2296-13-102

**Published:** 2012-10-13

**Keywords:** Insulin therapy, Multiple daily injections, Diabetes, Randomised, HbA1c, Psychosocial, Hypoglycaemia

## Abstract

**Background:**

People with T1DM and insulin-treated T2DM often do not follow and/or adjust their insulin regimens as needed. Key contributors to treatment non-adherence are fear of hypoglycaemia, difficulty and lack of self-efficacy associated with insulin dose determination. Because manual calculation of insulin boluses is both complex and time consuming, people may rely on empirical estimates, which can result in persistent hypoglycaemia and/or hyperglycaemia. Use of automated bolus advisors (BA) has been shown to help insulin pump users to more accurately meet prandial insulin dosage requirements, improve postprandial glycaemic excursions, and achieve optimal glycaemic control with an increased time within optimal range. Use of a BA containing an early algorithm based on sliding scales for insulin dosing has also been shown to improve HbA1c levels in people treated with multiple daily insulin injections (MDI). We designed a study to determine if use of an automated BA can improve clinical and psychosocial outcomes in people treated with MDI.

**Methods/design:**

The Automated Bolus Advisor Control and Usability Study (ABACUS) is a 6-month, prospective, randomised, multi-centre, multi-national trial to determine if automated BA use improves glycaemic control as measured by a change in HbA1c in people using MDI with elevated HbA1c levels (#62;7.5%). A total of 226 T1DM and T2DM participants will be recruited. Anticipated attrition of 20% will yield a sample size of 90 participants, which will provide #62;80% power to detect a mean difference of 0.5%, with SD of 0.9%, using a one-sided 5% *t*-test, with 5% significance level. Other measures of glycaemic control, self-care behaviours and psychosocial issues will also be assessed.

**Discussion:**

It is critical that healthcare providers utilise available technologies that both facilitate effective glucose management and address concerns about safety and lifestyle. Automated BAs may help people using MDI to manage their diabetes more effectively and minimise the risk of long-term diabetes related complications. Findings from a recent study suggest that BA use positively addresses both safety and lifestyle concerns; however, randomised trials are needed to confirm these perceptions and determine whether bolus advisor use improves clinical outcomes. Our study is designed to make these assessments.

**Trial registration:**

NCT01460446

## Background

Large clinical trials have shown that intensive management of glycaemia and other vascular risk factors can prevent or delay the development of microvascular and macrovascular complications in both type 1 diabetes (T1DM) and type 2 diabetes (T2DM) [1-4]. Achieving optimal glycaemic control in people with T1DM [1,2] and advanced T2DM [5] often requires intensive insulin therapy, which involves either use of insulin pumps or multiple daily insulin injections (MDI) [1,2,5]. Such therapies divide insulin doses into basal, prandial and corrective elements, which can be adjusted independently to achieve optimal results. Despite the benefits of intensive diabetes management, many people with T1DM and insulin-treated T2DM do not follow and/or adjust their insulin regimens as needed [6-9]. A recent survey of 331 people with T1DM showed that 64% of the participants assessed their prandial insulin need inappropriately [10].

A significant obstacle to intensive insulin management is fear of hypoglycaemia [11-14], which has detrimental effects on people’s willingness to effectively manage their diabetes, particularly in terms of appropriate insulin dosing (e.g., under-dosing of insulin to avoid hypoglycaemia). This can lead to poor metabolic control and subsequent poor health outcomes [14]. Other key contributors to treatment non-adherence are lack of self-efficacy and difficulties associated with insulin dose determination. Calculation of an insulin dose is a complex process that must take numerous factors into account, such as the current preprandial glucose level, grams of carbohydrate (CHO) to be ingested, insulin sensitivity, insulin-to-CHO ratio, and active insulin on board. Further, poor glycaemic control has been correlated with poor numeracy skills [15]. This may lead to an inability to count carbohydrates, errors in interpreting blood glucose (bG) results to determine correction doses and inaccuracies in calculating insulin doses based on insulin-to-CHO ratios.

Although many insulin pumps now feature automated bolus advisors, which automatically calculate bolus insulin dosages to cover carbohydrate (CHO) intake and address out-of-range bG levels based on individualised insulin parameter estimates, people using MDI therapy must perform these dosage calculations manually. However, because manual calculation of insulin boluses is both complex and time consuming, people may rely on empirical estimates, which can result in persistent hypoglycaemia and/or hyperglycaemia [16,17]. In addition, manual bolus calculation does not take into account the effect of the active insulin that remains from the initial bolus (insulin-on-board), which creates a high potential for errors, particularly when determining a correction bolus.

Studies have demonstrated that use of automated bolus calculators helps insulin pump users more accurately meet prandial insulin dosage requirements, improve postprandial glycaemic excursions, and achieve optimal glycaemic control with an increased time within target range [18,19]. It is, indeed, possible that such automated calculations may be a major source of the perceived benefits of pump therapy for many patients. For example, a study by Garg and colleagues [20] showed that use of a bolus advisor containing an early algorithm based on sliding scales for insulin dosing in people using MDI resulted in improved HbA1c levels. Results from a recent survey [21] suggest that use of an automated bolus advisor may reduce fear of hypoglycaemia, increase confidence in bolus calculation, improve ability to control bG levels and achieve glycaemic goals, create a sense of increased flexibility in lifestyle, and improve overall well being. In a small pilot study, Schmidt and colleagues [22] found that automated bolus advisor use, in conjunction with training in CHO counting and MDI therapy, improves treatment satisfaction. However, to date, no large randomised trials have been conducted to determine whether use of an automated bolus advisor can improve glycaemic control and promote greater adherence to therapy in people treated with MDI therapy.

We hypothesised that, in addition to reducing HbA1c, use of an automated bolus advisor in people treated with MDI therapy can increase the time bG stays within the target range, reduce the magnitude of post-prandial excursions, reduce the frequency/severity of hypoglycaemia, and improve psychosocial outcomes, including treatment satisfaction, social functioning and factors important to quality of life. We designed a study to test this hypothesis, using a new automated bolus advisor system that integrates bolus calculation into a bG meter.

## Methods/design

The Automated Bolus Advisor Control and Usability Study (ABACUS) is a 6-month, multi-center, multi-national, prospective, randomised, controlled study to assess the impact of automated bolus advisor use on clinical and psychosocial outcomes in poorly controlled (#62;7.5% HbA1c), MDI-treated T1DM and T2DM participants. The trial will be conducted at approximately 30 sites in the UK and Germany. All sites will have prior experience working with the bolus advisor prior to study initiation. All clinical investigators from the sites involved will be given detailed educational input regarding the device settings and adjustment principles (either using the automated bolus advisor or using more traditional ‘paper-copy’ (e.g., insulin-to-carbohydrate ratio/insulin sensitivity factor) at centralised study training sessions. The study protocol was approved by the National Research Ethics Service (Redditch, UK) and Ethik-Kommission der Ärztekammer Westfalen-Lippe und der Medizinischen Fakultät der Westfälischen Wilhelms-Universität Münster (Münster, Germany) and is in compliance with the Helsinki Declaration [23].

The primary outcome of the study is to determine if use of an automated bolus advisor is associated with a significant reduction in HbA1c over 6 months, compared with a group having the same diabetes educational background but with no access to an automated bolus advisor. The goal is to decrease HbA1c by #62;0.5%. Secondary outcomes include: 1) change in time spent within bG target range; 2) frequency and severity of hypoglycaemia; 3) change in magnitude of postprandial glucose excursions; 4) change in glycaemic variability parameters; 5) frequency of bolus advisor use; 6) frequency of participants’ adjustments to proposed bolus amounts; 7) self-monitoring of blood glucose (SMBG) test frequency; 8) change in participants’ therapy adherence and use of rule sets; and 9) participant self-care behaviours, and psychosocial outcomes including treatment satisfaction, social functioning and factors important to quality of life.

### Participants

The study will recruit 226 T1DM and T2DM patients who have been using MDI therapy for at least 6 months. Participants will be enrolled and randomised to the experimental (EXP) or control (CNL) groups; 113 participants in each group. This will lead to a total of 90 participants completing each arm at 6 months, assuming a drop-out rate of 20%.

Key inclusion criteria are: ≥18 years of age; T1DM or T2DM treated with MDI therapy for ≥6 months; HbA1c #62;7.5%; adjusts meal insulin doses based on CHO content of meal; and has completed CHO training within last 2 years. Key exclusion criteria are: NPH or pre-mixed insulin; treated with anti-diabetic agents (except metformin); use of fixed-dose therapy; or use of sliding scale insulin doses determined exclusively on specific bG results. The complete list of inclusion and exclusion criteria is presented in Table 1.

**Table 1 T1:** Inclusion and exclusion criteria

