**Exclusion Criteria:**	
· On a therapy regimen that conflicts with study:	
· NPH or pre-mixed insulin	
· Oral anti-diabetic agents, with the exception of metformin	
· Injectable anti-diabetic agents other than long-acting insulin and rapid-acting insulin analogs or regular insulin (e.g., fixed dose therapy)	
· Use of sliding scale insulin therapy that determines insulin dosages based exclusively on specific bG results	
· Participated in another interventional trial within 6 weeks prior to study	
· Diagnosed with any clinically significant infectious disease or major organ system disease, such as gastroparesis or renal disease (at Investigator's discretion)	
· Used systemic oral or inhaled steroids for more than 7 days within the last 3 months	
· On Chemotherapy or Radiation therapy (self-reported)	
· Pregnant or lactating or is currently planning a pregnancy	

Participants will be identified and recruited from the investigators’ established patient population or from within the patient population of other physicians within their group practice using the inclusion/exclusion criteria. Participants who agree to take part in the study and meet all of the inclusion but none of the exclusion criteria will be asked to sign the approved Informed Consent Form for the study.

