#### Visit 2: randomisation and intensive monitoring (week – minus 1)

At Visit 2, investigators will collect participants’ bG meters, completed 3-day glycaemic profiles and CGM devices (if applicable). Investigators will upload bG meter data via the research version of the Accu-Chek® SmartPix device (Roche Diagnostics, Indianapolis, Indiana, USA). When applicable, CGM data will also be uploaded to the server. Blood glucose data will be downloaded to clinic software, using either the commercial Accu-Chek® Smart Pix device or Accu-Chek® 360˚ View diabetes management system software (Roche Diagnostics, Indianapolis, Indiana, USA), and investigators will prepare printouts to review with each participant. New adverse events (AEs) and significant adverse events (SAEs), or changes in ongoing AEs/SAEs since the last visit, will be assessed and recorded; participants’ concomitant medications will be updated.

Investigators will then conduct MDI and CHO counting training, which will be individualised to address each participant’s knowledge and/or skills deficits as identified during the MDI therapy and CHO counting assessments performed at Visit 1. Standardised checklists will be used to document participant competencies. Participants must be competent in both MDI therapy and CHO counting knowledge in order to continue in the study. Following this training, participants will be randomised to the control group (CNL) for usual care or to bolus advisor use (EXP). EXP participants will be given automated bolus advisor training materials for review at home.

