#### Visit 3: training and therapy initiation (week – 0)

At Visit 3, investigators will collect participants’ bG meters, upload bG meter data to the secure server; download meter data to clinic software, and prepare printouts of bG data to review with participants. New AE/SAEs or changes to ongoing AE/SAEs since the last visit will be assessed and concomitant medications updated. Investigators will use the therapy parameter cards and instruct participants on how to use their parameters.

EXP participants will be given their automated bolus advisor device (Accu-Chek® Aviva Expert bG meter, Roche Diagnostics, Indianapolis, Indiana, USA) and instructed to discontinue use of their current bG meter. Investigators will conduct 1-hour training sessions in automated bolus advisor device use and update the devices with each participant’s new therapy parameters.

At the conclusion of the visit, all participants will receive SMBG supplies and a logbook with a 3-day glycaemic profile form. Participants will be instructed to complete the 3-day profiles one week prior to Visit 5.

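### Table 1 does not exclude people who already use an automated bolus advisor, so the eligibility criteria do not secure the no-access comparison, and the HbA1c difference may be biased toward zero

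*Protocol article*

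**What the plan says.** - Methods/design defines the primary comparison: the advisor group is "compared with a group having the same diabetes educational background but with no access to an automated bolus advisor".
- The same section says of the centres: "All sites will have prior experience working with the bolus advisor prior to study initiation".
- Participants says of eligibility: "The complete list of inclusion and exclusion criteria is presented in Table 1". The nearest item in Table 1 is the exclusion headed "On a therapy regimen that conflicts with study". Its sub-items cover insulin type, other anti-diabetic agents and sliding-scale dosing. No criterion mentions a bolus advisor or calculator.
- The paragraph after Table 1 gives the source of participants: "Participants will be identified and recruited from the investigators’ established patient population", or patients of other physicians in the same practice. Table 1 also requires at least 3 months in the practice.
- Visit 2 describes the control allocation: "participants will be randomised to the control group (CNL) for usual care".

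**The concern.** The control group is defined by one property, the absence of an advisor, and the list that decides who enters does not test for it. Someone on multiple daily injections who already doses with an advisor can meet every criterion, including the one on adjusting meal insulin to carbohydrate content. Usual care at a centre that knows the device does not by itself mean that the patient has none.

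The primary outcome is change in HbA1c from baseline. For an existing user allocated to EXP, whatever the advisor achieves is already in the baseline value, so little further change can be credited to allocation. An existing user allocated to CNL who carries on is not a no-access control. Among such people the two arms receive much the same thing, and including them pulls the overall difference toward zero. The same applies to time in range and the psychosocial scores. A modest observed difference would then be harder to read against the stated goal of more than 0.5%. The Discussion already fears that intensive management of both groups will narrow the difference, and this would add to it.

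**Working it through.** **Inputs.** From Primary outcome analysis: 90 per arm after 20% attrition, difference 0.5%, SD 0.9%, one-sided 5% two-sample t-test, power stated as above 80%. From Participants: 113 randomised per arm, 226 in all. The share p of existing users is not given and is an assumption here.

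**The plan's own figures.** 90 / (1 − 0.20) = 112.5, rounded up to 113 per arm, or 226, which matches. The standard error of the difference is 0.9 × √(2/90) = 0.134. By the normal approximation, power = Φ(0.5/0.134 − 1.645) = Φ(2.08) = 98.1%, and the noncentral t gives the same. The statement of more than 80% is true with a wide margin: 80% would need only 41 per arm.

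**Dilution.** Suppose a share p of each arm are existing users who continue, and their expected difference between arms is zero. The remaining 1 − p carry the full 0.5%. Then

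expected difference = (1 − p) × 0.5 + p × 0 = 0.5 × (1 − p).

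Power at 90 per arm, one-sided 5%, noncentral t:

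| p (assumed) | Expected difference | Power |
|---|---|---|
| 0% | 0.50 | 98.1% |
| 10% | 0.45 | 95.5% |
| 20% | 0.40 | 90.7% |
| 30% | 0.35 | 83.0% |
| 40% | 0.30 | 72.0% |
| 50% | 0.25 | 58.4% |

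**Where power reaches 80%.** The smallest difference with 80% power is (1.645 + 0.842) × 0.134 = 0.334 (normal approximation). The loss of contrast is then 1 − 0.334/0.5 = 33%.

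**How far the assumption can be pushed.** A zero contrast among existing users is an extreme case. Anyone enrolled has HbA1c above 7.5%, and EXP users would be retrained and given new parameters, so some further gain is possible. The pull toward zero also requires that CNL users continue. If they stopped on entering the trial, part of the contrast would return. For a given p, the table is therefore close to the worst case.

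**The case against.** The strongest reply is that nothing in the article shows existing users to be common. Site experience with the device is not ownership by patients. The Background calls the advisor system new and says people on injections calculate their doses by hand. That is the article's only statement on the matter, and it points to a small p. This stands as a reason to treat the size as unknown and perhaps small. It does not close the gap, because background text does not restrict entry, and the same section cites earlier studies of advisors in people on injections.

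A second reply is that a journal article condenses the protocol. That is fair for instructions to controls and for recording outside devices, whose absence here is no finding. It is weak against an eligibility list that the article itself calls complete.

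Third, former pump users add little. Table 1 requires at least 6 months on injections, so recent pump use is already ruled out, and a pump no longer worn cannot affect the control arm.

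A reader might also infer from Visit 3 that controls may keep an advisor of their own, because only EXP participants are "instructed to discontinue use of their current bG meter". The text does not support this. Both groups receive a study meter at Visit 1, and the meter that EXP gives up at Visit 3 is most naturally that one. CNL simply keeps the meter it was issued, so no parallel instruction would be expected. Issuing the advisor to EXP only, and taking CNL adherence from documented parameters and diaries, also point to an intended manual-calculation control.

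**Conclusion.** The eligibility gap is real. The primary comparison depends on controls having no advisor, and a list declared complete does not exclude people who already use one, at centres that all know the device. The consequence is conditional: if such people enrol and continue, the estimated HbA1c difference is biased toward zero by up to about their share of the arms, for example 0.05 at 10% or 0.10 at 20% on a true 0.5%.

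A reader might go further and conclude that the effect is diluted, or that a null result could not be interpreted. The documents support neither. They give no prevalence of use, and power stays above the stated 80% until about a third of the contrast is lost. The issue is the accuracy and interpretation of the estimate, not a failure of the sample size.

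**What to change.** Add one exclusion to Table 1: current use, or use within the 6 months before screening, of any automated bolus advisor or calculator, whether in a meter, a pump or an app. Six months matches the existing requirement on injection therapy. The cost is one screening question and a slightly smaller eligible pool where the device is already in use.

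If recruitment has closed, which is likely because the article expects findings in late 2012, record prior and concurrent advisor use in both arms. Keep the planned ITT analysis as primary and add a sensitivity analysis restricted to participants without advisor use at baseline. Define the restriction by baseline status only, so that the randomised comparison is preserved, and report use during the trial descriptively. The restriction costs little precision. At p = 20%, 90 × 0.8 = 72 per arm remain, against 71 needed for 95% power at 0.5%. At p = 30%, 90 × 0.7 = 63 remain, against 56 needed for 90%.

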**Inclusion Criteria:**	
· Must be 18 years of age or older	
· Diagnosed with Type 1 or Type 2 diabetes	
· Recent HbA1c #62;7.5% (measured within the last 6 weeks at local laboratory)	
· Using MDI therapy for at least 6 months consisting of 1–2 injections per day of long-acting basal insulin (Lantus® or Detemir®) and at least 2 injections per day of regular or rapid-acting analog insulin for meal coverage	
· Participant adjusts meal insulin doses based on carbohydrate content of meals	
· Participant with Type 2 diabetes may be on stable metformin therapy (therapy unchanged during 3 months prior to study)	
· Participant has been in Investigator's practice for at least 3 months; however may have been seen by another physician in the practice	
· Participant has completed carbohydrate (CHO) training within the last 2 years	
**Exclusion Criteria:**	
· On a therapy regimen that conflicts with study:	
· NPH or pre-mixed insulin	
· Oral anti-diabetic agents, with the exception of metformin	
· Injectable anti-diabetic agents other than long-acting insulin and rapid-acting insulin analogs or regular insulin (e.g., fixed dose therapy)	
· Use of sliding scale insulin therapy that determines insulin dosages based exclusively on specific bG results	
· Participated in another interventional trial within 6 weeks prior to study	
· Diagnosed with any clinically significant infectious disease or major organ system disease, such as gastroparesis or renal disease (at Investigator's discretion)	
· Used systemic oral or inhaled steroids for more than 7 days within the last 3 months	
· On Chemotherapy or Radiation therapy (self-reported)	
· Pregnant or lactating or is currently planning a pregnancy	

Participants will be identified and recruited from the investigators’ established patient population or from within the patient population of other physicians within their group practice using the inclusion/exclusion criteria. Participants who agree to take part in the study and meet all of the inclusion but none of the exclusion criteria will be asked to sign the approved Informed Consent Form for the study.

